Nowadays, the use of herbal medicine is proposed to be an adjunct to conventional antidiabetic treatments [25]. Medicinal plants contain glycosides, alkaloids, terpenoids, flavonoids, and carotenoids, which can exert antidiabetic effects [26]. Bitter almond gum is a key herb in Iranian medicine which is extracted from *Amygdalus scoparia* Spach. Remarkable in vitro antioxidant, antimicrobial, and antitumor effects of the water, methanol, and ethanol extracts of bitter almond kernels were demonstrated by Gomaa et al. [27]. Bitter almond gum increased the survival rate of *Lactobacillus acidophilus* La5 in tomato juice mixtures during fermentation, refrigeration, and exposure to gastric juice [28]. Bitter almond gum is an arabinogalactan polysaccharide that has prebiotic properties [29]. Bitter almond gum may have a favorable immune modulator effect possibly related to its prebiotic content [29]. To the best of our knowledge, there is only one study that evaluated the effect of bitter almond gum on metabolic parameters in overweight hyperlipidemic patients. In this study, bitter almond gum-enriched juice consumption significantly reduced body weight, body mass index (BMI), serum triglyceride (TG), hyperinsulinemia, and homeostatic model assessment for insulin resistance (HOMA-IR). We hypothesized that bitter almond gum, as adjuvant therapy, is able to improve metabolic, inflammatory, and oxidative stress biomarkers, as well as mental health in T2DM women.

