### Primary and secondary outcomes

Primary outcomes of the study will be FPG, glycosylated hemoglobin (HbA1c), and insulin. Secondary outcomes will include the lipid profile (total cholesterol (TC), high-density lipoproteins (HDL), low-density lipoproteins (LDL), TG), high-sensitivity C-reactive protein (hs-CRP), tumor necrosis factor-α (TNF-α), interleukin-1 (IL-1), interleukin-6 (IL-6), interleukin-10 (IL-10), interleukin-17 (IL-17), lipopolysaccharides (LPS), total antioxidant capacity (TAC), malondialdehyde (MDA), oxidative stress index (OSI), total oxidant status (TOS), superoxide dismutase (SOD), glutathione peroxidase (GSH-Px), catalase (CAT), soluble receptor for AGEs (sRAGE), carboxymethyl lysine (CML), pentosidine, 8-iso-prostaglandin F2α (8-iso-PGF2α), nitric oxide (NO), tryptophan (Trp), kynurenine (KYN), cortisol, glucagon-like peptide 1 (GLP-1), receptor for advanced glycation end products (RAGE), leptin, adiponectin, ghrelin, peroxisome proliferator-activated receptor (PPAR) gene expression, brain-derived neurotrophic factor (BDNF), endothelial cell adhesion molecules, plasminogen, cluster deference 4 (CD4), cluster deference 8 (CD8), anthropometric indices, blood pressure, dietary intake, and mental health. The following variables will be considered covariates: energy intake, weight changes, and the baseline values of glycemic indices, lipid profile, LPS, inflammatory and oxidative stress biomarkers, adipokines, and parameters related to mental health and the immune system. All variables will be measured at baseline and at the end of the study.

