### Clinical, para-clinical assessment

Demographic details and current use of medications will be recorded at baseline. Evaluation of patients’ physical activity level (PAL) will be done at the onset and end of the study using the International Physical Activity Questionnaire Short-Form (IPAQ-SF) [35]. The Depression, Anxiety, and Stress Scale (DASS) and a general health questionnaire (GHQ) will be used for assessing patient mental health [36, 37]. The DASS questionnaire consists of 14 items that are divided into three subscales to measure depression, anxiety, and stress [38]. Additionally, four other subscales (somatic symptoms, anxiety, insomnia, social dysfunction, and severe depression) will be assessed using the 28-item GHQ [39]. A 3-day food diary (one for a weekend day and two for 2 non-consecutive weekdays) [40] will be completed by patients at baseline and at the end of the study and applied for dietary assessment. Collected dietary records will be analyzed using the “Nutritionist 4” software (First Databank Inc., Hearst Corp., San Bruno, CA, USA).

At the start and end of the study, weight and height will be measured to the nearest 0.1 kg and 0.1 cm employing a reliable digital scale (Seca, Hamburg, Germany) and a meter mounted on the wall, respectively. A non-elastic tape will be placed on the midpoint between the lowest rib and the upper iliac crest to measure the waist circumference (WC) [41]. The hip circumference (HC) will be recorded at the maximum circumference over the hips without pressing the skin. Neck circumference (NC) will be measured at the level of the mid-cervical spine below the cricoid cartilage, and a minimum circumference will be calculated to the nearest 0.1 cm [42]. The BMI will be derived from weight (kg) divided by the square of the height (m^2^). All the anthropometric variables will be measured by the same person to minimize measurement errors. Blood pressure will be measured three times by a DinaMap Compact after 30 min of resting, and the mean of the three will be reported.

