### Statistical analysis

SPSS version 24.0 (SPSS Inc., Chicago, IL, USA) will be applied to analyze the data. Mean ± standard deviation (SD) or median (25th–75th percentile) and frequency (percentage) will be used to present quantitative and qualitative variables, respectively. The normality of our data will be assessed with the Kolmogorov-Smirnov test. Log transformation in the cases of non-normally distributed data will be done. In order to examine differences in qualitative and quantitative baseline variables between groups, we will apply the chi-square test and the unpaired Student *T*-test, respectively. To compare quantitative variables between groups, an analysis of covariance (ANCOVA) will be performed post-intervention. For within-group comparison, we will conduct the paired sample Student’s *T*-test or its nonparametric equivalent, the Wilcoxon test. To find the percentage difference, the absolute value of the change will be divided by the average of the values and multiplied by 100 [100 × (intervention values − placebo values)/placebo values]. *P* value < 0.05 will be considered statistically significant.

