## Discussion

This study is a randomized controlled trial to evaluate the usefulness of bitter almond gum as a functional food on the cardio-metabolic, immune-inflammatory, and oxidative stress biomarkers, as well as mental health in women with T2DM. Documented studies suggest the beneficial effects of consuming functional food on macro- and micro-vascular complications of T2DM [47–49]. It is well established that prebiotics exerts wide-ranging impacts on human health and disease. There are numerous studies on the positive effects of prebiotics on cancer, vascular diseases, obesity, and mental disorders [50]. Bitter almond gum, as a possible source of polyphenols and prebiotic fiber, might have anticancer, anti-inflammatory, antioxidant, antilipidemic, antimicrobial, antiviral, and immunomodulatory properties [51, 52]. A randomized study found that 6-week bitter almond gum consumption significantly decreased anthropometric measures and insulin resistance in hyperlipidemic patients [30]. Flavonoids and phenolic acids activate the PPAR gene [53]. PPAR activates the expression of genes encoding lipoprotein lipase (LPL) and apo C-II oxidation [54]. These mechanisms might play a role in the improvement of the lipid profile after bitter almond gum supplementation. On the other hand, bitter almond gum, as a prebiotic, improves glucose tolerance via an increase in GLP-1 secretion [55]. Studies on the effect of bitter almond gum on health are rare. Prebiotic compounds detected in bitter almond gum resemble gum Arabic in being composed of the arabinogalactan polysaccharide [29]. Babiker et al. reported the glucose and lipid-lowering effect of Arabic gum in patients with T2DM [56]. Ahmed et al. revealed that Arabic gum supplementation could downregulate adipose triglyceride lipase (ATGL) and super conserved receptor expressed in brain2 (SREB2) and upregulate hormone-sensitive lipase (HSL) gene expression in the liver of mice fed a high-fat diet [57]. The positive effects of Arabic gum in reducing oxidative stress and inflammation have also been shown [58, 59]. An animal study evaluated the effect of Arabic gum on inflammatory and oxidative stress biomarkers in the gastrointestinal tract of the experimental model of chronic kidney disease (CKD), lower levels of TNF-α, IL-6, transforming growth factor β1 (TGF-β1), lipid peroxidation, nitrite, and higher concentrations of IL-10, catalase, glutathione reductase, TAC, SOD, and nuclear factor erythroid 2–related factor 2 reported in the duodenal mucosa [60]. Other anti-inflammatory effects attributed to Arabic gum include blockage of the liver macrophage function, modulation of nuclear factor-kB, the maturation of dendritic cells (DCs), and consequent improvement of CD4+ T cell proliferation [61]. Arabic gum may directly scavenge free radicals or ROSs through the presence of various antioxidant compounds or by elevating the synthesis of antioxidant biomolecules [62, 63]. It is possible that Arabic gum can improve the antioxidant capacity due to the presence of amino acid residues such as lysine, tyrosine, and histidine, which show antioxidant properties [64, 65]. This trial is the first randomized, triple-blind controlled study investigating the effects of bitter almond gum consumption on the cardio-metabolic risk factors, oxidative stress, inflammatory biomarkers, LPS, CML, 8-iso-PGF2α, NO, Trp, KYN, cortisol, GLP-1, RAGE, leptin, adiponectin, ghrelin, BDNF, and mental health in women with T2DM. We hypothesize that bitter almond gum supplementation would improve cardio-metabolic, inflammatory, and oxidative stress indices and mental health through gut microbiota modulation in T2DM women.

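### Weight change, known only after randomisation, is named as an ANCOVA covariate, and energy intake is named without a time point, so the main comparison need not estimate the total effect of the gum

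*Protocol article*

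**What the plan says.** Under Primary and secondary outcomes, the protocol article lists its covariates: "The following variables will be considered covariates: energy intake, weight changes, and the baseline values of glycemic indices", followed by further baseline laboratory and mental-health measures. The restriction to baseline begins only with the third item, so it does not cover energy intake or weight change.

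The Statistical analysis section gives one between-group method: "To compare quantitative variables between groups, an analysis of covariance (ANCOVA) will be performed post-intervention". It names no covariates, so the list above is the only one in the document.

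On timing, the outcomes section says "All variables will be measured at baseline and at the end of the study". Energy intake comes from the 3-day food diary, which "will be completed by patients at baseline and at the end of the study and applied for dietary assessment".

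The secondary outcomes end with "anthropometric indices, blood pressure, dietary intake, and mental health". The Background says of the only earlier study of the gum on metabolic parameters that "bitter almond gum-enriched juice consumption significantly reduced body weight, body mass index (BMI), serum triglyceride (TG"), with falls in insulin and HOMA-IR as well. The Discussion says that "6-week bitter almond gum consumption significantly decreased anthropometric measures and insulin resistance in hyperlipidemic patients". Study design and participants describes a superiority trial analysed by intention to treat.

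**The concern.** An ANCOVA in a randomised trial gains precision from covariates fixed before allocation. A covariate that treatment may change does something else: the treatment coefficient then compares patients who had the same weight change, and allocation did not randomise that comparison.

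The protocol treats weight as something the gum may alter, since it measures anthropometry as an outcome and cites a weight reduction in its supporting study. It also plans to hold weight change constant when it estimates the gum's effect. Two things follow:

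- Any benefit for fasting glucose, HbA1c or insulin that acts through weight loss is taken out of the estimate.
- If something else drives both weight change and glycaemia (adherence to the diet and exercise advice is an obvious candidate), the adjusted comparison can show a difference where there is none.

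For weight itself the model degenerates. Week-8 weight equals baseline weight plus weight change, so with baseline weight also in the model nothing is left for treatment to explain.

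**Working it through.** **1. Is each variable post-randomisation?**

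- *Weight change: yes.* Weight is measured at the start and end of the study, so the change needs the week-8 value. A pre-trial change is not a sensible reading, because eligibility requires stable weight over the preceding three months.
- *Energy intake: not determined.* Diaries exist at both time points. Its place outside the baseline phrase suggests an on-study value, but the text does not say so.

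**2. What does the adjusted coefficient estimate?** Let *a* be the gum's effect on weight change (in SD) and *r* the within-arm slope of outcome on weight change, both scored so that benefit is positive. In a linear model:

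adjusted effect = total effect − *a* × *r*

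This equals the total effect only if *a* = 0 or *r* = 0. The documents give neither value, so all values below are assumptions.

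**3. Benchmark from the plan's own sample size.** The plan has 19 per group at 90% power, with 28.3 mg/dl for LDL and no SD. Two-sided, by the normal approximation, the implied standardised effect is (1.960 + 1.282) × √(2/19) = 1.05, so the SD is 28.3/1.05 ≈ 26.9 mg/dl. The 19 cannot be checked independently without the SD. It serves here only as a scale. Approximate power uses SE = √[(1 − r²)(2/19)(1 + a²/4)].

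| a | r | removed (a × r) | share of 1.05 | power (planned 90%) |
|---|---|---|---|---|
| 0 | any | 0 | 0% | not reduced |
| 0.3 | 0.2 | 0.06 | 6% | 87% |
| 0.5 | 0.3 | 0.15 | 14% | 81% |
| 0.5 | 0.5 | 0.25 | 24% | 79% |
| 0.8 | 0.5 | 0.40 | 38% | 58% |

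**4. Simulation with a smaller total effect** (0.80, residual SD 0.8, 19 per arm, least squares with and without weight change):

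| a | slope | share through weight | estimate without → with | power without → with |
|---|---|---|---|---|
| 0.3 | 0.2 | 0.06/0.80 = 7.5% | 0.80 → 0.74 | 83% → 77% |
| 0.8 | 0.25 | 0.20/0.80 = 25% | 0.80 → 0.60 | 82% → about 55% |
| 0.8 | 0.5 | 0.40/0.80 = 50% | 0.80 → 0.40 | about 71% → 28% |

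If the whole effect ran through weight, the adjusted estimate would be zero. That is a limiting case and is left out of the range.

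**5. No true effect on the outcome, but a shared cause.** If an unmeasured cause loads λ on both weight change and outcome (each with SD 1), then *r* = λ² and the adjusted effect is 0 − *a*λ².

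| a | λ | −aλ² | type I error |
|---|---|---|---|
| 0.8 | 0.3 | −0.07 | about 5% |
| 0.3 | 0.6 | −0.11 | about 6% to 7% |
| 0.5 | 0.6 | −0.18 | about 8% |
| 0.8 | 0.6 | −0.29 | about 13% (12.5% to 14% across runs) |

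Without adjustment the type I error stays at about 5% throughout.

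**The case against.** Four arguments can be made on the other side.

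- **Both variables are not shown to be post-randomisation.** A reader might infer that they are. The text supports this for weight change only. For energy intake the defect is an unstated time point, and stating that the baseline value is meant would cure it. This stands.
- **The evidence for mediation is thin.** A reader might take the Background and Discussion as two reports that the gum lowers body weight. Only the Background names body weight; the Discussion says anthropometric measures. Because the Background says there is only one such study, the two sections appear to describe the same one. It was in overweight hyperlipidemic patients taking gum in juice, not in women with type 2 diabetes taking powder. No section reports an effect of the gum on energy intake. This stands: weight is a plausible mediator and intake a speculative one.
- **The larger figures depend on adverse inputs.** The heaviest loss of power needs a 0.8 SD weight effect, and a type I error near 13% also needs a shared-cause loading of about 0.6. Milder inputs change little. This stands, so no single figure should be quoted as the expected bias.
- **The list may be a set of candidates.** Entering every listed baseline marker in a model with about 40 patients is hardly practicable, and the analysis section does not say how the list is used. This weakens any claim that the model will certainly adjust for weight change. It does not remove the point, because no other covariate set is given and nothing marks the adjustment as secondary or exploratory.

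**Conclusion.** The point holds for weight change as written. It is a post-randomisation variable, the protocol measures anthropometry as an outcome, and adjusting for it would not give the total effect under the intention-to-treat superiority framework. For energy intake the finding is narrower: the time point is unspecified.

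The size is unknown. With assumed weight effects of 0.3 to 0.8 SD, modest to strong associations and 19 per arm, about 6% to 50% of the effect is removed. Power falls from slightly to by more than half, and type I error lies between about 5% and 15%. If the gum does not change weight there is no bias.

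A reader might also infer that the bias must run towards zero. The documents do not support that, because shared causes can move the estimate either way. The case for changing the plan rests on what the model estimates rather than on any one simulated figure.

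**What to change.** In the covariate sentence under Primary and secondary outcomes, and correspondingly under Statistical analysis:

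- Limit the main ANCOVA to pre-randomisation covariates: the baseline value of the outcome being analysed, the stratification factors age and BMI and, if wanted, baseline energy intake.
- Delete weight change from the list.
- State that energy intake means the baseline value.
- Analyse week-8 weight and dietary intake as outcomes, as the protocol already lists them.
- If a weight-change-adjusted model is of interest, present it only as a labelled exploratory mediation analysis that states its assumption of no unmeasured shared causes.

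The cost is a wording change. Every value needed is already collected, and no stated sample-size figure changes. Trial status says that the trial has not yet started, so the change can be made before any outcome data exist, through the route under Protocol amendments.

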### Clinical, para-clinical assessment

Demographic details and current use of medications will be recorded at baseline. Evaluation of patients’ physical activity level (PAL) will be done at the onset and end of the study using the International Physical Activity Questionnaire Short-Form (IPAQ-SF) [35]. The Depression, Anxiety, and Stress Scale (DASS) and a general health questionnaire (GHQ) will be used for assessing patient mental health [36, 37]. The DASS questionnaire consists of 14 items that are divided into three subscales to measure depression, anxiety, and stress [38]. Additionally, four other subscales (somatic symptoms, anxiety, insomnia, social dysfunction, and severe depression) will be assessed using the 28-item GHQ [39]. A 3-day food diary (one for a weekend day and two for 2 non-consecutive weekdays) [40] will be completed by patients at baseline and at the end of the study and applied for dietary assessment. Collected dietary records will be analyzed using the “Nutritionist 4” software (First Databank Inc., Hearst Corp., San Bruno, CA, USA).

At the start and end of the study, weight and height will be measured to the nearest 0.1 kg and 0.1 cm employing a reliable digital scale (Seca, Hamburg, Germany) and a meter mounted on the wall, respectively. A non-elastic tape will be placed on the midpoint between the lowest rib and the upper iliac crest to measure the waist circumference (WC) [41]. The hip circumference (HC) will be recorded at the maximum circumference over the hips without pressing the skin. Neck circumference (NC) will be measured at the level of the mid-cervical spine below the cricoid cartilage, and a minimum circumference will be calculated to the nearest 0.1 cm [42]. The BMI will be derived from weight (kg) divided by the square of the height (m^2^). All the anthropometric variables will be measured by the same person to minimize measurement errors. Blood pressure will be measured three times by a DinaMap Compact after 30 min of resting, and the mean of the three will be reported.

A venous blood sample (10 mL) will be drawn from all participants following 10 to 12 h overnight fasting and centrifuged for serum isolation at baseline and at week 8 of the trial. FPG, lipid profile, and hs-CRP will be immediately determined after collecting samples. FPG and lipid profiles will be evaluated using the enzymatic colorimetric assay and commercial kits (Pars Azmoon, Tehran, Iran). The LDL will be derived from the Fried Ewald calculation [43]. The remainder of the serum samples will be stored at −70°C until the end of the study. Serum hs-CRP, TNF-α, IL-1, IL-6, IL-10, IL-17, LPS, CML, 8-iso-PGF2α, NO, Trp, KYN, cortisol, GLP-1, RAGE, leptin, adiponectin, ghrelin, BDNF, endothelial cell adhesion molecules, and plasminogen levels will be measured using an enzyme-linked immunosorbent assay (ELISA) kit. Flow cytometry and dual-color reagents will be applied to measure CD4 and CD8 (Dako Company, Denmark). HbA1c A will be determined using a high-pressure liquid chromatography D-10 system. Plasma insulin concentrations will be assessed using a chemiluminescent immunoassay method. TAC will be determined through the colorimetric method. Thiobarbituric acid reactive substances (TBARS) assay will be utilized to measure MDA levels using a spectrofluorometer [44]. The reverse transcription polymerase chain reaction (RT-PCR) will be used to determine the altered expression of the PPAR gene. The subsequent formulas will be used to calculate the oxidative stress index (OSI), the HOMA-IR, and the quantitative insulin sensitivity check index (QUICKI):OSI =100 × (TOS/TAC) [45]. Total oxidant statusHOMA-IR = [fasting insulin (μU/mL) × FPG (mM/L)] / 22.5QUICKI = 1/ (log (fasting insulin, μU/ml) + log (FPG, mg/dl)) [46].

### Data management

The study progress, protocol, validity, and integrity of the info, also as ethical requirements, will occasionally be supervised by a clinical trial monitor. All participants will be encouraged to answer the questions honestly. To analyze the data of the participants who withdraw from this trial for any reason, the ITT analysis will be used. All participants will be followed up for 8 weeks after the treatment assignment.

### Confidentiality

Each participant will be assigned a unique code number. All data will be stored on the drive and available only to the study team. Questionnaire data and consent forms will be stored on paper, remain separate from study data, and be coded with a particular code number.

### Statistical analysis

SPSS version 24.0 (SPSS Inc., Chicago, IL, USA) will be applied to analyze the data. Mean ± standard deviation (SD) or median (25th–75th percentile) and frequency (percentage) will be used to present quantitative and qualitative variables, respectively. The normality of our data will be assessed with the Kolmogorov-Smirnov test. Log transformation in the cases of non-normally distributed data will be done. In order to examine differences in qualitative and quantitative baseline variables between groups, we will apply the chi-square test and the unpaired Student *T*-test, respectively. To compare quantitative variables between groups, an analysis of covariance (ANCOVA) will be performed post-intervention. For within-group comparison, we will conduct the paired sample Student’s *T*-test or its nonparametric equivalent, the Wilcoxon test. To find the percentage difference, the absolute value of the change will be divided by the average of the values and multiplied by 100 [100 × (intervention values − placebo values)/placebo values]. *P* value < 0.05 will be considered statistically significant.

